### 1.12. Measure of Adherence

There are several methods to measure adherence going from the most subjective measures (self-reported adherence) to the most objective measures (biological markers). A review of the different measures of adherence to antiretroviral medications has been developed by Miller and Hays and includes self-reported adherence, clinician estimated adherence, diaries, pharmacy record, clinic attendance, plasma level and electronic monitors. Each measure presents some advantages and disadvantages, even the most objective one that consists in measuring the level of drug in blood sample. In fact, a main limitation of plasma level being that participants who are aware that adherence will be assessed will be more likely to use the product just before the adherence is being assessed. Evidence from the VOICE trial however shows that participants reported extremely high self-reported adherence (about 90%) but adherence assessed through plasma level was only 25% for vaginal PrEP and 30% for oral PrEP, justifying that plasma level may provide in the context of PrEP an unbiased measure of adherence. Another method for assessing adherence is through the use of the Medication Event Monitoring System (MEMS) Track caps, an electronic monitoring method. The caps have a microelectronic circuit that registers the exact dates and times of all bottle openings, thus providing more detailed information about the timing of doses than can be obtained through most other methods.

## 2.0 Study Method

This is a demonstration project to evaluate the effectiveness of three models for the delivery of PrEP and TasP as part of a combination prevention strategy for serodiscordant couples in three states in Nigeria. The overall goal is to identify the best model to facilitate uptake of PrEP as part of a comprehensive HIV prevention package for the HIV negative partner in serodiscordant relationships whose HIV positive partner has not begun ART or

---

has been on ART for less than six months. PrEP (daily oral FTC / TDF) will be offered to the HIV-1 uninfected partner. Uptake of PrEP and TasP and adherence to PrEP will be measured. Factors (individual, facility and community level) that facilitate PrEP and TasP uptake and adherence to PrEP will also be assessed.

HIV-1 infected participants will be offered the opportunity to use ART support services regardless of their CD4 count. This is in line with the current national guidelines on HIV treatment for adults and adolescents (2010:13). The current guidelines enable HIV positive individuals in discordant relationships to have access to ART irrespective of the CD4 count. This project will therefore serve as a measure of the effectiveness of this program in Nigeria.

For each couple, if the HIV-1 infected partner initiates ART, we will discontinue PrEP for the HIV-1 uninfected partner six months later (once viral suppression is typically achieved). If the HIV-1 infected partner declines to initiate ART, or initiates and discontinues, we will continue PrEP. Mixed-methods work will be conducted to understand user preferences, couples decision-making, and barriers to uptake of and adherence to both PrEP and ART.

In Cross River State, PrEP will be provided through the outpatients department. The model will evaluate the effectiveness of integration of PrEP service delivery using an integrated approach for access and uptake of both PrEP and TasP services for both HIV negative and the index partners.

In Plateau State, PrEP and TasP will be provided through a decentralized service delivery model. PrEP related service will be obtained from a secondary health facility for the first three months as this is considered a critical period in any care program. Thereafter, services would be decentralized to primary and private project satellite clinics (primary and private centres). The satellite centres will provide the three monthly HCT services and monthly drug refill services. Six monthly laboratory assessment of health profiles would however, be conducted at the central hospital.

In Anambra State however, all PrEP and TasP services will be provided through HIV treatment centres with services remaining centralized.

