## 5.0 Study Sites

The ART sites currently supported by FHI360/SIDHAS and the Harvard/PEPFAR projects will be considered. These sites are the Federal Medical Centre at Nnewi in Anambra State, the Federal Medical Centre in Calabar, Cross Rivers State and the University of Jos, Plateau State. The use of ART sites for study conduct is important so as to ensure ART access by HIV positive partners who are eligible for ART.

One approach to programmatic scale-up of PrEP access within the public sector health service in Nigeria is to integrate its provision into existing service delivery. Integrating HIV prevention into routine outpatient services has several advantages, including:

- Clients would be able to access care and services without undue stigma that is associated with attendance of special clinics like the HIV clinic. Outpatient services are widely available in Nigeria
- The model would enable the project learn about how to provide HIV services as an integrated health care service which can facilitate unbiased attention to both male and females who attend the hospital for health care.

Integrating HIV prevention into HIV care services also has several advantages, including:

- Trained specialized care providers who understand HIV care and service provision would learn to incorporate PrEP and TasP into existing HIV prevention, treatment and care services.
- The HIV index partner can be better managed and monitored over the long term.

Empirical evidence is needed to assess whether integrating PrEP provision into outpatient care services and HIV treatment services can achieve similar levels of safety and PrEP use as observed in the various clinical trials. The study design however, would enable real time changes to be made to implementation plans based on outcomes of the formative assessments as more effective strategies for PrEP access by study populations are identified.

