## 8.0 Sample Size

A total of 600 couples will be enrolled from the three study sites. Enrollment will be competitive. All couples will participate in the longitudinal cohort study. A subset of up to 60 couples per site will be invited to participate in qualitative in-depth interviews and focus group discussions.

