### 13.0 Data management and analysis

#### 13.1 Data analysis

A Statistical Analysis Plan (SAP) will be developed. This will outline the planned analyses. Any deviations to be made from the plan will be documented in the SAP.

For the primary objective 3.1.1, the outcome variable to be measured will be the uptake of antiretroviral-based HIV-1 prevention program. Data collected will include all sero-discordant couples recruited into the study and will be followed up longitudinally. The number of new infections averted through the use of PrEP and TasP by sero-discordant couples who accessed the ARV preventions compared with those who had access to programs but did not use the tools will be documented. The impact of various variables such as age, viral load of partner, region, coital act, use of condom on uptake of PrEP and TasP and on HIV sero-conversion will also be assessed.

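### Each delivery model runs at one site in one state, so a difference in uptake between models cannot be told apart from a difference between sites, and the goal of identifying the best model should be restated as description

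*Protocol*

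**What the plan says.** Section 2.0 says the project will "evaluate the effectiveness of three models for the delivery of PrEP and TasP as part of a combination prevention strategy" and then sets the aim: "The overall goal is to identify the best model to facilitate uptake of PrEP as part of a comprehensive HIV prevention package". It allocates the models as follows:

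- "In Cross River State, PrEP will be provided through the outpatients department"
- "In Plateau State, PrEP and TasP will be provided through a decentralized service delivery model"
- "In Anambra State however, all PrEP and TasP services will be provided through HIV treatment centres with services remaining centralized"

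The Summary gives three sites in three states, and Section 5.0 names one in each of Anambra, Cross River and Plateau. Section 1.8 records that the implementation models came out of consultative meetings. Nothing in the protocol describes random assignment.

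Other provisions bear on the comparison. Objective 3.2.1 lists centralized against decentralized drug access among the facility-level factors to assess. Section 13.1 will examine the effect of "age, viral load of partner, region, coital act, use of condom on uptake of PrEP and TasP" and on seroconversion. Section 10.0 lets each site design its own recruitment and screening methods within the common eligibility rules. On enrolment of the 600 couples, Section 8.0 says "Enrollment will be competitive". Objective 3.1.1 schedules formative evaluations at months 6, 12 and 18 that may modify the programme, and Section 5.0 says the design "would enable real time changes to be made to implementation plans based on outcomes of the formative assessments".

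**The concern.** Choosing the best of three models is a comparative claim. To support it, the data must show how much uptake differs between models beyond what would be seen between hospitals running the same model. Here no model runs in two states and no state runs two models. Any gap in uptake could reflect the model, the hospital and its staff, the state's population, or the locally designed recruitment. The data contain nothing that separates these.

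The same limit applies to centralized against decentralized access in Objective 3.2.1 whenever that factor is judged by comparing states. Because the programme may also be revised during follow-up, a label such as decentralized may not mean the same service throughout. What is at stake is the conclusion that readers would carry forward: an apparent winner among the models could be no more than the best of three hospitals.

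**Working it through.** **Inputs from the protocol.** Three models (Section 2.0), three sites with one per state (Summary, Section 5.0), 600 couples in total (Section 8.0). The protocol gives no expected uptake, between-site variance or test for this goal, so there is no stated figure to reproduce.

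**Step 1: aliasing.** Write uptake as an intercept plus model indicators plus site indicators. With three models and three sites, that is 1 + 2 + 2 = 5 columns. Each model indicator equals a site indicator, so the matrix has rank 3, the same as with model alone. The two sets of effects cannot be separated.

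**Step 2: error term.** Degrees of freedom for sites within models = sites − models = 3 − 3 = 0. Site-to-site variation cannot be estimated, and a model effect has no valid yardstick. More couples per site do not change this. Plateau's satellite clinics and Anambra's treatment centres do not help either, because they lie within one state and one model.

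**Step 3: what ignoring this could do (illustration only).** Assumptions, none of them in the protocol: uptake 70%, 200 couples per site (600/3), three equally good models, true site rates varying with standard deviation s.

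- Sampling variance of a site's rate: 0.7 × 0.3 / 200 = 0.00105, a standard deviation of 3.2 points.
- Site variation inflates the three-group chi-square statistic (2 df) by about F = 1 + s²/0.00105.
- Rejection at the 5% level is then about 0.05^(1/F), because the upper tail of a chi-square on 2 df is exponential.

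| s (points) | F | Approximation | Simulation |
|---|---|---|---|
| 0 | 1.00 | 5% | 5% |
| 2.5 | 1 + 0.000625/0.00105 = 1.60 | 15% | 15% |
| 5 | 1 + 0.0025/0.00105 = 3.38 | 41% | 41% |
| 10 | 1 + 0.01/0.00105 = 10.52 | 75% | 76% |

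**Step 4: picking a winner (illustration only).** Suppose one model is truly better, 80% against 70% for the other two. In simulation with 200 couples per site, it has the highest observed uptake 98% of the time with no site variation. This falls to 84%, 75% and 63% at intraclass correlations of 0.01, 0.02 and 0.05. At 70% uptake those correspond to site standard deviations of √(0.21 × ICC) = 4.6, 6.5 and 10.2 points.

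**Step 5: does competitive enrolment make it worse?** With an assumed split of 350/200/50, the simulated rejection rates are 13%, 35% and 69% at s = 2.5, 5 and 10 points, lower than with equal sites. Imbalance costs precision: the standard error of a pairwise difference is √(0.21 × (1/200 + 1/200)) = 4.6 points for 200 against 200, and √(0.21 × (1/350 + 1/50)) = 6.9 points for 350 against 50. That is a separate matter from the aliasing.

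**The case against.** The strongest reply is that this is a demonstration project, not a comparative trial. Objective 3.1.1 evaluates an implementation model in the singular, and the Summary speaks of constructing one. The evaluation is mixed-method and uses quality improvement, so a programme judgement need not rest on a significance test between sites. Section 13.1 describes no between-model test or ranking rule; it compares couples who used the interventions with those who did not and adds covariates. Eligibility is common to all sites, and Section 11.7 standardizes retention efforts. Programme changes are a declared purpose of the design.

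Most of this stands, and it limits the point to the goal sentence in Section 2.0 and the related factor in Objective 3.2.1. It does not remove it: that sentence does promise to identify the best model, and nothing in the protocol confines it to description. This is not a detail to leave to an analysis plan, because no analysis plan can supply replication that the design lacks.

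A reader might infer more than the protocol supports:

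- **That nothing can be learned about the models.** Uptake, retention, adherence and cost can be described at each site. A comparison is possible too, but only by assuming no site effects.
- **That the protocol plans a test with an inflated error rate.** It states no such test. The percentages in steps 3 and 4 rest on assumed uptake, site sizes and site variation.
- **That competitive enrolment aggravates the problem.** Step 5 shows that it does not. Section 11.4 also lets the investigators reassign targets across sites, so site sizes are not left wholly to chance.
- **That 'region' should be deleted from Section 13.1.** Section 13.1 contains no model term for it to remove. In pooled analyses of age, viral load or condom use, region can absorb site differences. It only needs correct reading.
- **That Plateau's move to satellite care after three months rescues the comparison.** Set against the other two sites, that change still rests on one transferring site, has a short period before transfer (visits at month 1 and then quarterly, Section 11.0), and coincides with time on PrEP.

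**Conclusion.** The point holds as a mismatch between the stated overall goal and the design. Model and site or state are fully aliased, with no degrees of freedom for sites within models, so a difference in uptake cannot be credited to the model without assuming zero site effects. This follows from the allocation alone and needs no numerical assumption. The illustrative rejection rates of about 15%, 41% and 76% show only how misleading a naive comparison could be under the stated assumptions; they are not error rates of a planned analysis. The primary objectives are not comparisons and are not undermined by this point. It should be fixed, and rewording is enough.

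**What to change.** 1. **Section 2.0.** Replace the aim of identifying the best model with a descriptive evaluation of uptake, retention, adherence and cost of each model as implemented at its site. Report site-specific 95% confidence intervals and state that between-site differences will not be attributed to the model. Apply the same limit to centralized against decentralized access in Objective 3.2.1 when it is judged between states.
2. **Section 13.1.** Keep region as a site adjustment, and state that its coefficient is a combined site-and-model effect.
3. **Objective 3.1.1 and Section 5.0.** Date each programme change made after a formative evaluation, so that results can be described by version.

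The cost is protocol wording, a log of changes and a more modest claim. Keeping the comparative goal would instead require each model to run at several sites, which is a different and much larger study.

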## Summary

Multiple studies have established that anti-retroviral drugs could be used to reduce the rate of infection in a population in two different ways, known by the acronyms TasP (Treatment as Prevention) and PrEP (Pre-Exposure Prophylaxis).

TasP targets people who are already infected with HIV-1, reducing their infectiousness in the population. Multiple studies have established that, after about the first six months of treatment, Anti-Retroviral Therapy (ART) reduces HIV-1 concentrations to undetectable levels in blood plasma and genital compartments. Additional studies have demonstrated that HIV transmission by an infected person is significantly reduced when that person adheres to ART well enough to maintain viral suppression.

PrEP targets people who are not infected with HIV-1. The PrEP strategy supplies a drug that, taken regularly by an uninfected person, reduces the probability of becoming infected on exposure to the HIV-1 virus. (A familiar similar strategy is the "sunday-sunday pills" used to prevent malaria.) Multiple studies have demonstrated that adherence to a PrEP regime works.

Although it will collect data relevant to efficacy, it is not the purpose of this study to establish the efficacy of TasP and PrEP. That work has been done and, for this study, the efficacy of these strategies is presumed established. The open issue with TasP and PrEP is how to implement the strategies in a large population as part of a comprehensive public health program aimed at preventing HIV infection. What are the barriers to uptake; that is, why would people hesitate to adopt a prevention strategy? What are the barriers to adherence; that is, what would prevent a person who has started PrEP or ART from continuing it? What are the most cost-effective ways of delivering, not just the drugs, but the counseling and support needed to make the strategies work? Should there be a separate program? Is it better done within an established program?

If this demonstration project is successful, we will have in hand a practical plan for the establishment of a comprehensive national program to prevent HIV infection in Nigeria.

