### 3.0 Objectives

#### 3.1 Primary objectives

- 3.1.1 Optimize, implement and evaluate the effectiveness of an implementation model which integrates PrEP and TasP provision into existing service provision centres.
- 3.1.2 Estimate the cost and cost effectiveness of the PrEP and TasP demonstration project.
- 3.1.3 Model the resources needed to provide scaled up PrEP and TasP access for serodiscordant couples in Nigeria.

**Objective 3.1.1: To optimize, implement and evaluate the effectiveness of an implementation model which integrates PrEP and TasP provision into existing service provision centres.**

The demonstration project will be evaluating the effectiveness of a model of HIV service delivery to couples that promotes and ensures effective PrEP access. Such a model should be able to ensure effective community engagement in ways that improve and support a couple's access and uptake of HIV prevention and treatment interventions, ensure access in hard to reach areas where there are few health facilities, and support sustained quality and consistency of PrEP and TasP services irrespective of place of delivery. The model for delivery of ART based HIV intervention programs for couples for this demonstration project would be designed based on feedback received during the formative research conducted to support this research. The study outcome should help critical stakeholders know how well the study model was able to achieve the desired PrEP service delivery into family planning services. This will help inform decision making on how to institutionalize the program, strategies that are economical and efficient, and how best to make modifications to the program implementation model to increase effectiveness.

The primary outcome of this objective is the measure of the impact that project intervention had on serodiscordant couples' access, uptake and retention in the antiretroviral-based HIV-1 prevention program. Formative and summative evaluations would be conducted. Formative evaluation will be conducted at months 6, 12 and 18 with derived information use to modify the program so as to increase its efficiency. The summative evaluation will be conducted at the end of the project and would help to decide on the effectiveness of the program.

*The primary measure of this objective will be the number of new infections averted by the use of PrEP and TasP.*

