**3.2 Secondary objectives**

- 3.2.1 Assess client, facility and community level factors influencing demand, preferences, uptake and adherence for antiretroviral-based HIV-1 prevention in Nigeria
- 3.2.2 Assess user preferences among high-risk HIV-1 serodiscordant couples for ART initiation for HIV-1 infected partners and PrEP for HIV-1 uninfected partners.
- 3.2.3 Ascertain initiation of and adherence to PrEP among HIV-1 uninfected partners as a bridge to ART.
- 3.2.4 Look for evidence of risk compensation by HIV-1 serodiscordant couples on PrEP or TasP, migration from condom use.
- 3.2.5 Determine the ART resistance profile developed by HIV-1 serodiscordant couples on PrEP during the study; assess that profile's prevalence.
- 3.2.6 Model the resources needed to provide PrEP and TasP for other specific target groups who are also at high risk of contracting HIV.

**Objective 3.2.1: Assess client, facility and community level factors influencing preferences, uptake and adherence for antiretroviral-based HIV-1 prevention in Nigeria**

Understanding factors that influence couples' preferences and their likelihood to initiate and adhere to PrEP and/or ART in a real-world setting is critical for providers who will counsel HIV-1 serodiscordant couples.

Using interviewer-administered questionnaires, assessments will be made of the correlates to preferences, uptake and adherence to ART and PrEP. These will include characteristics of sexual risk (e.g., sexual frequency, condom use, whether the HIV-1 uninfected partner reports outside partners); depression and substance use; gender of the HIV-1 uninfected partner; fertility intentions; partnership characteristics (whether the couple is cohabiting at baseline, has children, is together throughout follow-up, whether members have other partners, and whether the HIV-1 infected partner initiates ART), and clinical characteristics of the HIV-1 infected partner (e.g., CD4 count, WHO stage).

Facility level factors would be assessed. This would include the impact of training on quality of service delivery and perceived changes by clients at the service sites, effective communication strategies, adherence counselling, use of centralized vs decentralized services for drug access, time spent and costs for travels to facility. The study shall also assess the impact of use of home self-test kits (OralQuick®) for partner recruitment and uptake of PrEP and TasP by serodiscordant couples. See the attached Protocol B.

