#### 11.5 Monitoring adherence and safety

At enrollment, HIV-1 testing will be performed for HIV-1 uninfected partners, to confirm eligibility (HIV-1 seronegative at the time of study start). Couples will be counseled about ART and PrEP. HIV-1 uninfected partners will be offered PrEP; HIV-1 infected partners will be counseled about ART guidelines and will be offered TasP, or referred/initiated on ART if they are eligible at the time of enrollment. HIV-1 infected partners will continued to be counseled on the use of TasP as long as (s)he is eligible to use TasP during the study period. HIV-1 uninfected partners who have symptoms potentially consistent with acute HIV-1 infection (fever, rash, pharyngitis) will have enrollment deferred for 2 weeks at which time repeat serologic testing will be performed (and, if positive, will result in study exclusion).

Adherence, risk reduction and contraceptive counseling will be completed. Adherence of HIV-1 uninfected participants will be measured by self-report and pill counts. In addition, the MEMS cap would be used to complement data generated in the clinic on self-reported pill use. The MEMS cap would generate information on the daily use of pill through electronically capturing data on the frequency of opening the drug bottles. Outcomes of the adherence profile generated from self-reported pill counts and the MEMS cap would be used to counsel patients on how to improve or adhere to drug-use adherence patterns.

Additionally, behavioral and medical history data as well as data on participant preferences regarding antiretroviral-based prevention strategies and fertility intentions will be collected during one-on-one interviews with staff counsellors. Physical examinations for both members of the couple will be conducted. For the woman, physical examination will include pelvic examinations, including naked eye examination of the external genitalia and speculum examination of the vagina and cervix. For males, physical examination will be limited to naked eye examination of the external genitalia.

Syndromic diagnosis and management of STIs will be done. Counseling and clinical care for STIs at the study sites will be in accordance with the Federal Ministry of Health's guidelines. Participants with STIs will be encouraged to refer their partners for treatment.

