At enrollment HIV-1 uninfected women will have a pregnancy test to confirm eligibility (must not be pregnant to complete enrollment). Women will be asked about pregnancy at every scheduled follow-up visit and pregnancy testing will be done when clinically indicated (e.g., missed menses, participant request); PrEP will be continued during pregnancy and breastfeeding. In addition, pregnant women will be advised to continue with their follow up visits. When these participants no longer have a positive pregnancy test, the pregnancy outcome will be documented.

Every 6 months, in addition to regular quarterly visit procedures, CD4 counts and plasma viral loads will be done for HIV-1 infected partners.

Clinical safety will be assessed pre-, during- and post-enrollment. Laboratory safety assessments will be done at enrollment, month 12, study exit and additionally if indicated. At these visits, blood samples will be collected for urea, electrolytes, creatinine, liver function tests, full blood count, calcium and phosphate levels.

All HIV-1 infected partners who are interested in starting ART independent of their becoming eligible for ART under the current national guidelines, will be offered ART. Once the HIV-1 infected partner has been using ART for 6 months, PrEP will be discontinued for the HIV-1 uninfected partner, after counseling to the couple.

During follow-up, HIV-1 infected and uninfected participants will complete a quantitative interview to capture evolution in preferences to uptake of antiretroviral-based HIV-1 prevention and fertility intentions and any risk compensation behaviours. Questionnaires will be administered separately to both members of couples.

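### Objective 3.2.1 needs ART adherence but only PrEP adherence has a defined measure, and TasP enters the Objective 3.1.1 outcome as uptake with no suppression condition although viral load is already scheduled

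*Protocol*

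**What the plan says.** On what is needed: Objective 3.2.1 says that "assessments will be made of the correlates to preferences, uptake and adherence to ART and PrEP", using interviewer-administered questionnaires. Section 2.0 says of ART access for index partners at any CD4 count that "This project will therefore serve as a measure of the effectiveness of this program in Nigeria". For Objective 3.1.1, "The primary measure of this objective will be the number of new infections averted by the use of PrEP and TasP". The Summary explains that ART lowers transmission when "that person adheres to ART well enough to maintain viral suppression".

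On what is measured: Section 2.0 states "Uptake of PrEP and TasP and adherence to PrEP will be measured". Section 11.5 states "Adherence of HIV-1 uninfected participants will be measured by self-report and pill counts", with MEMS caps as a supplement. Objective 3.2.3 and Section 11.3 also tie pill counts and MEMS data to PrEP.

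On analysis: Section 13.1 says that for Objective 3.1.1 "the outcome variable to be measured will be the uptake of antiretroviral-based HIV-1 prevention program". It then plans to compare infections averted between couples who used the antiretroviral tools and couples who had access but did not use them. The partner's viral load is listed among the variables whose influence on uptake and seroconversion will be assessed.

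On viral load: Section 11.5 says that every six months "CD4 counts and plasma viral loads will be done for HIV-1 infected partners". Section 6.0 lists only six-monthly CD4 counts for the same partners.

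**The concern.** For TasP, the state that protects the uninfected partner is viral suppression, not the start of ART; the Summary says so. The protocol also treats adherence to ART in this population as an open question. Section 1.1 calls it unclear whether asymptomatic people will keep the commitment to adherence seen in advanced disease. Section 1.5 lists sustained adherence among the critical unanswered questions. Section 1.4 reports that modelled impact depended strongly on consistent use of the drugs.

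A plan that records TasP as uptake, and asks about ART adherence by questionnaire alone, leaves that question without an objective outcome. Two results are exposed. The first is the ART-adherence part of Objective 3.2.1. The second is any TasP coverage figure used in the Objective 3.1.1 comparison or passed to the Objective 3.1.2 model.

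**Working it through.** The protocol has no figure to reproduce here, so the check sets the sections side by side.

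| Construct | PrEP, uninfected partner | ART/TasP, index partner |
|---|---|---|
| Uptake | Sections 2.0 and 13.1 | Sections 2.0 and 13.1 |
| Adherence wanted | Objectives 3.2.1 and 3.2.3 | Objective 3.2.1 |
| Adherence measure defined | Self-report, pill count, MEMS (Objective 3.2.3; Sections 11.3 and 11.5) | None; questionnaire for correlates (Objective 3.2.1) and mixed-methods work on barriers (Section 2.0) |
| Adherence support | Sections 11.9 and 11.10 | Sections 11.10 and 11.11 |
| Biological marker | None named | Viral load every six months (Section 11.5) |
| Role of the marker in the analysis | Not applicable | Covariate for uptake and seroconversion (Section 13.1) |

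Section 11.9 collects adherence data at each visit by brief interview, but its text is about use of the study product and PrEP. The only objective marker for the index partner is therefore viral load, and no section makes it an outcome.

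**Who counts as uptake.** Section 7.3 admits index partners who are on ART with a viral load above 5000 copies/ml, and Section 4.0 likewise describes index partners on ART who are not suppressed. Such a person is on ART and unsuppressed at enrolment. Section 13.1 attaches no suppression condition to uptake, so nothing in the text keeps this person, or a later starter who does not become suppressed, out of the user group.

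**Consequence in symbols.** Let u be the proportion of index partners recorded as TasP uptake and f the proportion of those who are unsuppressed.

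- Coverage by uptake = u
- Coverage by suppression = u × (1 − f)
- Difference = u − u(1 − f) = u × f

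For the user versus non-user comparison, leave aside PrEP in the same couple. Let the infection rate be r0 in non-users, rs in partners of suppressed users and rn in partners of unsuppressed users, with f weighted by person-time.

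- User-group rate = (1 − f) × rs + f × rn
- Contrast = r0 − [(1 − f) × rs + f × rn] = (1 − f)(r0 − rs) + f(r0 − rn)

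If rn is close to r0, the contrast shrinks to about (1 − f) times the contrast for suppressed users. The two uses therefore err in different ways. In the internal comparison the effect per user is diluted, and the result cannot show whether TasP failed or was never achieved. Multiplying that diluted contrast by the number of users does not by itself inflate the total averted. Overstatement arises if coverage u is paired with an effect that presumes suppression, as a cost-effectiveness model might do. The protocol gives neither u nor f, so no number follows.

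**The case against.** The strongest reply is that suppression is both observed and analysed. Viral load is taken at screening (Section 11.4) and every six months (Section 11.5), it is a named explanatory variable in Section 13.1, and an unsuppressed ART user can be identified from planned data. Objective 3.2.1 names an instrument for ART adherence, and mixed-methods work covers barriers to it. Tabulations and cut-offs are normally left to the statistical analysis plan. The emphasis on PrEP also fits the overall goal in Section 2.0, which is to find the best model for PrEP uptake.

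Much of this stands, and it limits what may be claimed. Four stronger readings are tempting and are not supported:

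- **Such a partner is scored as a TasP success.** No section defines a TasP success. The person counts as uptake, and a transmission would still be recorded as a seroconversion.
- **Uptake is the only result for TasP.** Objective 3.1.1 also names access, retention and infections averted, and Section 13.1 adds seroconversion.
- **The ART-adherence part of Objective 3.2.1 cannot be answered.** A questionnaire is named. The weakness is that it is subjective and yields no defined variable. Section 1.12 reports about 90% self-reported adherence against 25% to 30% by plasma level in one trial, but that was PrEP and does not transfer directly to ART.
- **ART starts will be the model input.** Objective 3.1.2 says only that intermediate project outcomes will feed the model.

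What the reply does not remove is that the protocol itself, not a later plan, fixes what is measured (Section 2.0) and the outcome variable for Objective 3.1.1 (Section 13.1). Those statements fit poorly with Objective 3.2.1 and pass over a better measure that is already scheduled. A covariate for uptake and seroconversion is not a TasP outcome.

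**Conclusion.** The point holds as a mismatch between objectives and measures. ART adherence is wanted, but only PrEP adherence has a defined measure. TasP enters the Objective 3.1.1 outcome variable as uptake without regard to suppression, and the six-monthly viral load is left as a covariate. The stated method is weaker than one the protocol could use from data it already plans to collect.

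The size is unknown. The coverage gap is u × f, and the protocol supplies neither term; any percentage would rest on assumptions from outside it. The conclusion assumes that uptake in Section 13.1 carries no unstated suppression condition and that viral loads are taken as Section 11.5 says rather than as Section 6.0 lists. It concerns measurement only and takes no position on when PrEP should stop.

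**What to change.** 1. In Section 2.0, Objective 3.2.1 and Section 13.1, name viral suppression at the six-monthly viral load as the objective outcome for ART adherence and TasP, with one analysis cut-off for all sites. The 5000 copies/ml in Section 7.3 is an eligibility limit and should not be taken as that cut-off by default. The questionnaire can stay as a supplement.
2. Report TasP as started and as started and suppressed, by site and by time on ART. Time on ART matters because the Summary expects suppression only after about six months. Show ART users with no viral load as a separate category, since Section 6.0 does not trace participants for routine visits.
3. Use the suppressed proportion wherever TasP coverage enters the Objective 3.1.1 comparison or the Objective 3.1.2 model.
4. Reconcile Section 6.0 (six-monthly CD4 only) with Section 11.5 (CD4 and viral load).

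The cost is wording and a little more analysis. Under the Section 11.5 schedule no new visits or samples are needed. The downside for the project is a less favourable TasP figure.
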